### Implementing Lynch syndrome evidence into practice

Lynch syndrome (LS) is one of the genetic syndromes that has been impacted by these implementation challenges. LS is an autosomal dominant cancer predisposition syndrome conferring an increased risk of colorectal, endometrial and other cancer types [26]. Identifying individuals affected by LS allows access to cancer risk management strategies (e.g. colonoscopic surveillance, risk-reducing hysterectomy) proven to reduce cancer incidence and improve survival [27, 28]. Despite guidelines recommending universal LS screening strategies for patients with LS-associated cancers, the condition remains largely underdiagnosed and current genetic referral rates are suboptimal [11]. In Australia, little is known about LS diagnostic pathways or the practices hindering rates of referral - partially owing to the challenges of linking data between hospitals, pathology providers and familial cancer clinics [29], as well as a lack of standardised referral pathways upon which these data can be mapped to identify system failures. Whilst Brennan and colleagues identified various stages at which cases of colorectal cancer (CRC) slipped through the LS referral cracks in hospitals in the Australian Capital Territory [11], further work is needed to establish practices at a national level.

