#### Post-implementation outcomes

The primary post-implementation quantitative outcome will be the change in the proportion of patients with risk-appropriate completion of the site-specific LS tumour testing and referral pathway within 2 months of CRC resection. Secondary outcomes will be (1) proportion of high risk-patients who were referred to the FCCs (sensitivity of referral), (2) proportion of referred patients who attended FCC and (3) proportion of patients with missing testing and referral data.

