#### Assessing clinical practice change

The analysis of each dichotomous study outcome will be conducted at the individual patient level, using generalised estimating equation (GEE) adjustment for the clustering of patients within hospital networks. We will estimate the adjusted relative proportion (RR) of patients with the outcome using a generalised linear regression model with Poisson distribution, log link and robust standard errors. The exposure variable will be the implementation intervention status of the respective hospital network at the time of the patient’s CRC resection (pre or post implementation-intervention). We will carry out a two-sided test for each outcome, with the significance threshold defined using the Bonferroni correction for the number of outcomes tested. Missing testing and/or referral data will be treated as tests not carried out, or referral not completed, respectively. As covariates, we will consider time period (3-month intervals), time since implementation of intervention strategies (3-month intervals), patient age at operation, sex and cancer stage. The Quasi-Akaike information criterion will be used to select which covariates to include in the final model. To account for non-independence of within-hospital outcomes, all GEE analyses will be carried out with exchangeable working correlation structures. We will carry out sensitivity leave-one-out analyses by individually excluding hospital networks that accounted for more than 20% of the total patient numbers. If private patient status can be reliably obtained in at least six of eight trial sites, a supplementary analysis will be performed using private patient status as an additional covariate.

We note previous studies have found that a small number of clusters can lead to inflated type I error rates, and so-called small-sample corrections have been proposed to address this. However, these small-sample corrections were found to be too conservative for eight clusters [46]. Consequently, we will carry out a supplementary analysis using small-sample correction only for those outcomes that are robustly significantly associated with the implementation intervention status.

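### Scoring missing records as not done lets a change in record completeness move the pre/post relative proportion with no change in care

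*Protocol article*

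**What the plan says.** The rule is in the protocol article under Assessing clinical practice change: "Missing testing and/or referral data will be treated as tests not carried out, or referral not completed, respectively". It is stated without distinction by outcome, period or arm. The exposure in the same model is the intervention status of the hospital network at the time of resection ("pre or post implementation-intervention"), and the estimate is a relative proportion.

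Under Post-implementation outcomes, the primary outcome is the "change in the proportion of patients with risk-appropriate completion of the site-specific LS tumour testing and referral pathway within 2 months of CRC resection". It covers all resected patients, not only those at high risk. The third secondary outcome is the "proportion of patients with missing testing and referral data".

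On data capture, Pre-implementation outcomes describes a retrospective collection covering 24 months before the study. Clinical data collection describes collection during the intervention and for up to 9 months after the intervention strategies end. The Implementation Leads, who also run the intervention, extract the data.

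The supporting analyses named are leave-one-out exclusion of large networks, a private-patient covariate and a small-sample correction. None of them varies the handling of missing data.

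**The concern.** By making missingness an outcome, the article treats a missing record as different from a step that was not done. The analysis rule then merges the two inside the primary outcome. The Background gives a reason to keep them apart: it says little is known about diagnostic pathways in Australia, "partially owing to the challenges of linking data between hospitals, pathology providers and familial cancer clinics". A record that cannot be found may therefore reflect linkage rather than care.

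This matters because the model contrasts two periods with different data capture. If records become more or less complete from one period to the next, the rule turns that change into apparent better or worse care. The pilot described in the Background achieved standardised pathology report wording without more referrals overall, so reporting can change while the target outcome does not. At stake is whether an RR above 1 can be read as improved practice.

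**Working it through.** **No plan figure to reproduce.** The article gives no missingness rates, no baseline completion rate and no high-risk share, and it defers the power calculation until baseline data exist. All rates below are assumptions, shown as ranges.

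**1. Effect on the pre/post RR.** Let true completion be *p* in both periods. Let a share *m* of patients have a missing record, unrelated to care, that is scored as failure. Observed completion is *p*(1 − *m*), so

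spurious RR = (1 − *m*_post) / (1 − *m*_pre), and *p* cancels.

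This applies to missing test data in any patient and to missing referral data in high-risk patients.

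| Missing, pre to post | Calculation | Spurious RR |
|---|---|---|
| equal in both | – | 1.00 |
| 10% to 5% | 0.95/0.90 | 1.06 |
| 15% to 5% | 0.95/0.85 | 1.12 |
| 20% to 10% | 0.90/0.80 | 1.125 |
| 30% to 10% | 0.90/0.70 | 1.29 |
| 5% to 10% (a rise) | 0.90/0.95 | 0.95 |

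Example for 15% to 5% with *p* = 70%: 0.70 × 0.85 = 59.5% and 0.70 × 0.95 = 66.5%, ratio 1.12.

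**2. Could this reach significance?** Study site recruitment gives 100–250 resections per network per year. Eight networks over 2 years give 1,600–4,000 patients pre; over 0.75 year they give 600–1,500 post. Take α = 0.05/4 = 0.0125 (assumed, since neither the base level nor the number of outcomes tested is stated) and the usual normal approximation for two independent proportions. The chance that a 20% to 10% fall in missingness is declared an effect is then:

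- *p* = 30%: 15% to 42%
- *p* = 50%: 35% to 80%
- *p* = 70%: 68% to 99%

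These figures ignore clustering, so they indicate order of magnitude only.

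**3. Effect on the arm comparison.** The ratio of the two arms' spurious RRs is what matters.

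- Same change in both arms: 1.00.
- 20% to 5% in one arm and 20% to 15% in the other: (0.95/0.80) / (0.85/0.80) = 0.95/0.85 = 1.12.

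**4. Direction by type of missing data.** Assume that success for a low-risk patient means tested and not referred. Let *h* be the high-risk share, *T* = 80% tested, *s* = 50% of high-risk patients referred, and *f* the share of low-risk patients referred.

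- True completion: *T*[*hs* + (1 − *h*)(1 − *f*)]
- With missing tests: the same, multiplied by (1 − *m*)
- With missing referrals: *T*[*hs*(1 − *m*) + (1 − *h*)(1 − *f*(1 − *m*))]

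With *h* = 10%, *f* = 10%, *m* = 20%:

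- True: 0.8 × (0.05 + 0.81) = 68.8%
- Missing tests: 0.8 × 68.8% = 55.0%
- Missing referrals: 0.8 × (0.04 + 0.828) = 69.4%

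Among tested patients, missing referral data lower high-risk success from 50% to 40% and raise low-risk success from 90% to 92%. Over *h* = 5–15% and *f* = 5–10%, 20% missing referral data move the whole-cohort figure by between −0.5 points (70.6% to 70.1%) and +1.1 points (70.4% to 71.5%). The same share of missing tests lowers it by 13 to 15 points.

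**The case against.** Scoring missing as not done is a common audit convention, and it may be largely right here. Each cluster includes its own pathology laboratory and familial cancer clinic (FCC), and a local Implementation Lead searches those databases, so no entry may well mean no test or referral. The remark on linkage is background on national knowledge, not a description of this trial's records. Both periods are extracted by the same role, and a retrospective baseline is not shown to be less complete. The third secondary outcome would make a shift in missingness visible. Sensitivity analyses may stand in an analysis plan that is not shown.

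Much of this stands, and it limits the point to a conditional one. What remains is that the article itself fixes the rule, and that making a shift visible does not remove it from the primary RR.

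Four stronger readings are tempting but not supported:

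- **Missingness is expected to fall.** The article lists it as an outcome and says nothing about direction.
- **Low-risk patients gain from missing data.** This holds only for missing referral data, and only if non-referral counts as risk-appropriate for them, which the article does not spell out. Missing test data make them fail.
- **The theory versus non-theory comparison is biased.** An equal change in both arms leaves it unbiased.
- **The rule makes the first secondary outcome, referral among high-risk patients, run the wrong way.** One can build such a case: 40 of 60 tested patients referred before and 60 of 95 after is a fall from 67% to 63%, although referrals per 100 truly high-risk patients rise from 40% to 60%. That shows dependence on who is tested, and would occur with complete records. The article does not define high risk, so it is also not established that an untested patient can never be classed as such.

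**Conclusion.** The concern holds in a limited form. The rule merges recording with care in the pre/post contrast, and no analysis stated in the article tests how much that matters. If missing test data, or missing referral data in high-risk patients, change between periods, the RR moves by (1 − *m*_post)/(1 − *m*_pre): 1.06 to 1.29 over the assumed falls, and below 1 if missingness rises. The arm comparison is affected only by a change that differs between arms, for example a ratio of RRs of 1.12. Missing referral data have a small whole-cohort effect whose sign depends on the risk mix, so the rule cannot be defended as uniformly conservative.

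The sizes assume that missingness is unrelated to care. Where no record really does mean no care, the bias is smaller. This is a cheap improvement, not a flaw that invalidates the design.

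**What to change.** Before extraction starts, have the extraction tool code each testing and referral step without a positive record as either *source searched, not done* or *record unavailable*. The third secondary outcome already implies some such distinction.

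- Keep the not-done rule as the primary analysis for the first code.
- For the second, pre-specify sensitivity analyses: multiple imputation within network and period, plus best-case and worst-case bounds. Imputation alone is not enough, because it usually assumes data missing at random, which is doubtful if absent records go with absent care.
- Show missingness by period and arm beside the primary result, and qualify the conclusion if its direction depends on the handling.
- Keep the stated denominators of the first two secondary outcomes, and report how many patients have unknown risk status because no test result is available. Re-basing them on all resections would change what they measure: the first would become a crude referral rate that rewards referring low-risk patients, and the second would merge attendance with referral.

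The cost is one extra code and modest extra analysis; Trial status says data collection has not commenced. The downside is a more qualified conclusion if records are poor, since the bounds can be wide. With 50% completion among available records and 20% then 10% unavailable (assumed), the pre proportion lies between 40% and 60% and the post proportion between 45% and 55%. The extreme RRs are 0.45/0.60 = 0.75 and 0.55/0.40 = 1.375.

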### Outcomes

#### Pre-implementation outcomes

CRC surgery, pathology, and familial cancer clinic (FCC) clinical data will be retrospectively collected across all hospital networks for patients admitted during a 24-month period prior to study commencement, to demonstrate LS referral pathway clinical practice. The data will be cross-referenced with LS referral maps to be constructed for each hospital network. The proportion of patients who transition to each step, in adherence to the pathway map will be calculated, leading to the identification of bottlenecks. The referral maps and bottlenecks will be compared across hospital networks, with particular attention to potential differences in processes between geographical regions. A validated TDF-based questionnaire (Influences on Patient Safety Behaviours Questionnaire) [37] will be used to quantitatively evaluate psychosocial barriers to risk-appropriate completion of the LS referral pathway. Qualitative focus group data will be used to understand key barriers in context.

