## Measures

### Clinical data collection

Patient-level clinical practice data relating to the CRC and LS referral pathway will be extracted from relevant surgical, pathology, and FCC databases by the Implementation Leads (see Additional file 2 for variables). Patient data will be collected throughout the implementation of the intervention, and outcome data will be collected for up to 9 months after the end of the intervention strategies. Patients will be eligible for inclusion if they undergo CRC resection at participating hospital networks within the time periods for data collection and are aged over 18 years at the time of resection. Given the short duration of the trial and minimal risk of harm, a formal data monitoring committee will not be required. An ethics-committee-approved data management plan has been presented to research governance officers and will be refined for each participating hospital network to ensure compliance with site-specific protocols.

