### Trial status

This study commenced in July 2017. Hospital networks have been approached to participate, have been randomised and are engaged in the governance process. Formal recruitment of hospital networks will be complete when research governance applications are approved. Recruitment of individual participants for the research activities described in phases 1–7 has not commenced, and data collection has not commenced.

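### The two time covariates overlap with the pre/post exposure, so letting an information criterion choose them lets the data decide what the headline relative proportion means

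*Protocol article*

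**What the plan says.** All references are to the protocol article.

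- **Exposure** (Assessing clinical practice change): "The exposure variable will be the implementation intervention status of the respective hospital network" at the time of resection, coded pre or post. The section names no arm term.
- **Time covariates** (same section): "we will consider time period (3-month intervals), time since implementation of intervention strategies (3-month intervals"), alongside age, sex and stage. All are candidates, and the Quasi-Akaike criterion picks those in the final model. The article does not say whether the time terms are categorical or linear.
- **Pre window** (Pre-implementation outcomes): clinical data are collected retrospectively across all networks "for patients admitted during a 24-month period prior to study commencement".
- **Start date** (Trial status): "This study commenced in July 2017". At the time of writing the governance process was still under way and "data collection has not commenced". The article cites a registration of 27 June 2018, so it was written after that date.
- **Implementation** (Phase 6; Clinical data collection): the package is implemented over 6 months, and "Patient data will be collected throughout the implementation of the intervention".
- **Follow-up** (Clinical data collection): the post window is limited separately, in that "outcome data will be collected for up to 9 months after the end of the intervention strategies".

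**The concern.** The headline relative proportion (RR) is the coefficient of a pre/post indicator. Both time covariates carry part or all of the same information, so whether and how they enter changes what that coefficient measures.

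- If no 3-month interval contains both pre and post patients, a set of quarter indicators reproduces the pre/post indicator exactly. Software then drops a column, and the printed RR compares one post quarter with one reference quarter.
- If calendar time enters as a straight line, the RR is the jump left after the line has been carried over a period without data.
- If neither time term is selected, the RR is a plain before-after ratio with no allowance for secular trend.
- If time since implementation enters linearly, the RR refers to the first moment of implementation, not to the post period as a whole.

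Each of these could be reported under the same name, the adjusted RR. A fit criterion would choose among them, and it does not ask which quantity was wanted.

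**Working it through.** The article gives no sample size, power or RR for this outcome, so there is no figure to reproduce. The check is algebraic: is the pre/post column outside the span of the other columns?

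**Inputs from the article.** Eight networks; 24 months of baseline = 8 quarters; 6 months of implementation + 9 months of follow-up = 15 months = 5 post quarters.

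**Assumed.** Patients during implementation count as post. The gap between baseline and go-live is 3 to 7 quarters. The low end comes from the Implementation Lead's 24-month term: 24 − 6 − 9 = 9 months, or 3 quarters, for phases 1–5. The high end adds the 4 quarters from July 2017 to the registration date: 4 + 3 = 7. Network-quarters are weighted equally.

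**1. Calendar quarter as categories.** The pre/post term is estimable only if its column adds to the rank.

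| Layout | Shared quarters | Rank / columns | Pre/post estimable |
|---|---|---|---|
| Common baseline, common start after 3-quarter gap | 0 | 13 / 14 | no |
| Common baseline, starts staggered over 4 consecutive quarters | 0 | 16 / 17 | no |
| Network-specific baseline ending 3 quarters before start, starts up to 3 quarters apart | 0 | 19 / 20 | no |
| Same, starts up to 4 quarters apart | 1 | 21 / 21 | yes |
| Pre data run up to staggered starts | 3 | 20 / 20 | yes |
| Pre data run up to a common start | 0 | 16 / 17 | no |

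These results do not depend on cluster sizes or the intra-cluster correlation.

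**2. Calendar time as a straight line.** With n0 pre and n1 post quarters, d the distance between their mean quarters and W the within-period sum of squares of time, the variance inflation factor of the pre/post term for a common start is

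VIF = 1 + [n0·n1/(n0+n1)]·d²/W.

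Here n0·n1/(n0+n1) = 8 × 5/13 = 3.077 and W = 42 + 10 = 52.

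- Gap of 3 quarters: d = 13 − 3.5 = 9.5; VIF = 1 + 3.077 × 90.25/52 = 6.34.
- Gap of 7 quarters: d = 13.5; VIF = 1 + 3.077 × 182.25/52 = 11.8.
- Pre data continuous to a common start: n0 = 11, d = 8, W = 110 + 10 = 120; VIF = 1 + 3.4375 × 64/120 = 2.83.
- Pre data continuous to staggered starts (computed directly): 2.46.

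**3. How far the RR can move.** Illustration with true RR 1 and an assumed yearly rise during baseline that flattens afterwards. Let s be the log rise per quarter. The unadjusted log RR is 8s − 3.5s = 4.5s. The fitted slope is s × 42/52, so the trend-adjusted log RR is 4.5s − (42/52)·s·d.

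- 5% per year: s = ln(1.05)/4 = 0.0122. Unadjusted RR = 1.06. Adjusted RR = 0.96 (3-quarter gap, d = 9.5) or 0.93 (6-quarter gap, d = 12.5).
- 10% per year: s = 0.0238. Unadjusted RR = 1.11. Adjusted RR = 0.93 or 0.88.

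The same null data give a ratio above or below 1 according to whether the trend term is selected.

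**4. Time since implementation.** With a level for each of the five post intervals and pre as reference, the indicators sum to the pre/post indicator, so it is aliased in all six layouts. With linear coding, log mean = α + β·post + γ·k·post for k = 0 to 4. Then β is the effect at k = 0, while the average post effect is β + 2γ.

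**5. Arm-by-period term.** With calendar quarter categorical and common to both arms, it is estimable in all six layouts, with the networks in each pair of start dates split between arms.

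**The case against.** **The gap is an inference.** A reader might conclude that pre and post patients never share a quarter and that the adjusted RR is therefore not estimable. The article does not say so. That conclusion needs the commencement in the baseline definition to be the July 2017 project start. Governance approval is network by network, exposure follows each network's own status, and data are also collected during implementation. Staggered go-lives with continuous pre data would give shared quarters and an estimable effect. This stands, and the calendar-time part of the point is conditional on it.

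**Coding belongs in the analysis plan.** A pre/post indicator, running time and time since implementation together form an ordinary linear segmented model, which is full rank even with a gap. This is also right, and unstated coding is not a fault in itself. It does not remove the point: in that model the pre/post coefficient is a time-zero effect and, with a gap, an extrapolated one.

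**The criterion may drop the time terms.** Then the RR is estimable, but it carries no trend adjustment. That is a third meaning, and the article lets the data choose it.

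**The between-arm question is unaffected.** The arm-by-period contrast is indeed estimable throughout. The stated exposure, however, is pre/post status, and that is the coefficient affected.

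**Conclusion.** The point holds in conditional form.

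- On the literal windows, categorical calendar quarter is exactly aliased with pre/post. A linear trend identifies the RR only by extrapolation, with a VIF of about 6 to 12 for gaps of 3 to 7 quarters.
- If pre data run up to staggered go-lives, calendar quarter is estimable and the VIF falls to about 2.5 with linear time.
- Whatever the windows, time since implementation is either aliased with the exposure (a level for every post interval) or, if linear, changes the RR into a start-of-implementation effect.

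The documents do not support a flat statement that the analysis cannot be done. They do support saying that the meaning of the headline RR is left to a fit criterion. The VIFs rest on the assumed gap and equal weights. The RRs of 0.88 to 1.11 are an illustration under an assumed trend, not a forecast. Trial status reports that data collection had not begun, so the wording could be settled before any outcome was seen.

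**What to change.** Change the wording in Assessing clinical practice change:

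1. Exclude time since implementation from the model that gives the headline RR. Use it only to describe the course within the post period.
2. Do not let the Quasi-Akaike criterion select the time terms.
3. Base the effectiveness conclusion on an arm-by-period ratio from a model with calendar quarter common to both arms. Keep the pre/post main effect, and let software drop it only if it is truly aliased. Removing it by rule because the quarters absorb it is unsafe. With pre data continuous to staggered go-lives, a common log RR of 0.30 and no arm difference, omitting it gives a spurious arm-by-period ratio of about 1.09 to 1.11; keeping it gives 1.00.
4. If the pre and post windows share no quarters, report the pooled pre/post RR as a before-after ratio not separated from secular trend.

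The cost is analysis-plan wording, a more modest label on the pooled RR, and a less precise adjusted contrast. No change to data collection is needed.

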#### Phase 6 - support staff to implement interventions

Intervention strategies generated in phase 5 will be implemented using general implementation science principles (i.e. the need for management support and commitment among target group members, use of boundary spanners, flexibility driven by local context, incorporation into established structures) [16]. With a template provided by the research team, Implementation Leads will create a report that will outline findings from phase 1–5, the intervention package and a plan for implementation. This will be submitted to senior management from departments affected by any proposed intervention strategies (e.g. CRC surgery, pathology and FCCs), and may require revision based on management feedback. Once management approves the proposed implementation plan, intervention strategies will then be presented to relevant forums (e.g. MDT meetings, pathology team meetings) to gain feedback that will allow the development of a broader structure to disseminate findings. The Implementation Lead will then work collaboratively with the Implementation Team to implement the intervention package over a 6-month period.

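### QIC is allowed to decide whether calendar time and time since implementation enter the model, so the data choose what the pre/post RR estimates

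*Protocol article*

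**What the plan says.** The section on assessing clinical practice change (Protocol article, Analysis plan) specifies a "generalised linear regression model with Poisson distribution, log link and robust standard errors", fitted by GEE, and "all GEE analyses will be carried out with exchangeable working correlation structures". On the contrast it says: "The exposure variable will be the implementation intervention status of the respective hospital network", pre or post, at the time of the patient's resection. On adjustment: "As covariates, we will consider time period (3-month intervals), time since implementation of intervention strategies (3-month intervals), patient age at operation", together with sex and stage. It then adds: "The Quasi-Akaike information criterion will be used to select which covariates to include in the final model". On testing: "We will carry out a two-sided test for each outcome, with the significance threshold defined using the Bonferroni correction" for the number of outcomes.

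No time term is forced in, and nothing requires the same terms for every outcome. The article does not give the coding or origin of time since implementation, or say how the exposure RR is to be read if that term is kept.

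Phase 6 has the team "implement the intervention package over a 6-month period". The clinical data collection section gathers patient data throughout implementation and outcome data for up to 9 months after it, whereas Phase 7 takes its post-intervention data after the 6 months. Whether roll-out months count as post is therefore open.

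**The concern.** Age, sex and stage adjust a contrast whose meaning stays fixed. The two time terms change the contrast:

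- Status alone gives the crude post/pre ratio, with any secular trend included.
- Adding calendar time gives the step beyond the trend.
- Adding time since implementation, with its origin or reference at the first post interval, gives the effect at the start of the post period.

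QIC ranks models by fit and has no regard for which of these is the question. The stated primary outcome is the change in the proportion completing the pathway, which is not an effect at time zero. Selection could also settle on different terms for different outcomes, so that RRs held to the same Bonferroni threshold would answer different questions. A package rolled out over 6 months may well act gradually, and that is the shape for which the choice matters most.

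**Working it through.** **The plan's own figure.** None to reproduce: the article defers its power calculation until baseline data are available.

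**Inputs from the protocol.** Eight networks; 100 to 250 resections per network per year; 24 months of baseline data; 6 months of roll-out; up to 9 months of follow-up.

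**Assumptions.** Contiguous quarters, 24/3 = 8 pre and (6 + 9)/3 = 5 post; baseline proportion 0.40; between-network SD 0.15 on the log scale; threshold 0.05/4 = 0.0125 for one primary and three secondary outcomes.

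**Step 1: what each model targets.** Number the post quarters k = 0 to 4 and let the effect be RR(k) = 1.5^(k/4), that is 1.000, 1.107, 1.225, 1.355, 1.500.

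- Average post RR: 6.187/5 = 1.24.
- Time since implementation with origin at the first post quarter: RR(0) = 1.00.
- Numbered from 1, so the coefficient is extrapolated back one quarter: 1.5^(-1/4) = 0.90.
- Centred on the post period: 1.5^(2/4) = 1.22.

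Simulation (100 runs) gave 1.234 for status alone and 1.000, 0.905 and 1.221 for the three codings. Categorical coding with the first post interval as reference gave 0.997.

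**Step 2: what calendar time does.** Mean quarter is 3.5 pre and 10 post, a gap of 6.5. With no effect and a 2% per quarter rise (log scale), status alone targets exp(0.02 × 6.5) = 1.139.

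With the ramp and no trend, let b = ln(1.5)/4 = 0.1014. On an equally weighted log scale the common slope is 10b/(42 + 10) = 0.192b, where 42 and 10 are the within-period sums of squares of quarter. The status coefficient is 2b - 6.5 × 0.192b = 0.75b, so RR = exp(0.076) = 1.08. The simulated Poisson value was 1.064. A linear calendar term therefore absorbs part of a ramp.

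**Step 3: simulation of the stated analysis.** Patient-level Poisson GEE, exchangeable correlation, robust SE, linear time terms with origin at the first post quarter (TSI = time since implementation), lowest QIC of four models, 200 runs per row.

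| Truth | Status | + calendar | + TSI | + both | QIC kept TSI | Selected RR (median) |
|---|---|---|---|---|---|---|
| Ramp 1.0 to 1.5 | 1.235 | 1.064 | 0.999 | 0.998 | 100% | 1.001 |
| Ramp 1.0 to 1.25 | 1.119 | 1.042 | 1.001 | 1.003 | 95% | 1.002 |
| Ramp 1.10 to 1.5 | 1.296 | 1.146 | 1.100 | 1.097 | 99% | 1.096 |
| Step 1.25 | 1.247 | 1.252 | 1.247 | 1.251 | 40% | 1.253 |
| No effect, 2% per quarter trend | 1.139 | 1.001 | 1.093 | 1.000 | 41% | 1.002 |

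Rejection at 0.0125, in row order:

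- Status alone: 100%, 78%, 100%, 100%, 94%.
- Status plus calendar time: 11%, 8%, 47%, 88%, 9%.
- QIC-selected: 7%, 7%, 37%, 93%, 12%.

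With staggered starts and the 1.0 to 1.5 ramp, the selected RR was again about 1.00 (rejected in 11%).

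**Step 4: false positives under the trend.** QIC dropped calendar time in 6% + 7% = 13% of runs. Overall rejection at 0.0125 was 12%, against 9% with calendar time forced in. Two further simulations at 0.05 gave 17% against 13%, and 13% against 8% (calendar time dropped in about 8% of runs in the latter). The excess is 3 to 5 points.

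**Step 5: a narrower post period.** If post means only the 9 months after roll-out and the effect rises from 1.2 to 1.4 (150 runs), the selected RR was 1.21, rejected in 85% at 0.05, against 1.31 for status alone.

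**The case against.** A reader might infer that a building effect would simply be reported as no effect. The documents do not support that. It needs four things together: time since implementation is selected; its origin or reference is at the first post interval; the effect starts near RR 1.0 with roll-out counted as post; and only the exposure coefficient is read. The article fixes none of these, and coding is commonly left to an SAP. Centred coding gives 1.22, a start at 1.10 gives about 1.10 (understated, not null), the narrower post period gives 1.21, and a pure step is unaffected. This stands, and it limits the claim to understatement that can reach the null.

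A reader might also infer that forcing calendar time brings back the near-certain detection seen with status alone. It does not. For a 1.0 to 1.4 ramp, status alone gave about 1.20, whereas status plus linear calendar time gave 1.06 to 1.07 and was rejected in only 22% to 31% of runs. Nor is the false-positive problem large overall: QIC usually keeps calendar time when there is a trend. Much of the remaining excess over nominal is present even with calendar time forced in; the article itself acknowledges inflation with few clusters.

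Finally, eight clusters might seem too few for many time parameters. That limits joint tests of several coefficients and does not prevent testing the single exposure coefficient.

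What the objection leaves standing is the selection rule. It is written in the article, and an SAP would have to contradict it to remove it.

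**Conclusion.** The point holds in this form: the plan lets a fit criterion choose the estimand of its headline RR, possibly differently for each outcome. With a building effect and first-interval origin, the reported RR can fall from about 1.2 to about 1.0; with other codings or post windows it is attenuated less or not at all. With a secular trend and no effect, selection adds about 3 to 5 percentage points to the false-positive rate compared with forcing calendar time. These sizes depend on the assumed baseline proportion, between-network variation, effect shape, contiguous quarters and post window, none of which the article gives. That the RR changes meaning with the terms kept does not depend on them.

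**What to change.** Amend the section on assessing clinical practice change as follows:

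1. State the target effect, for example the average post-period RR adjusted for secular trend, and say whether roll-out months count as post.
2. Force one parsimonious calendar-time term, such as linear in quarters, into the primary model for every outcome.
3. Move time since implementation to a pre-specified secondary model of how the effect builds. Alternatively keep it with fixed coding, for example centred on the post period, so that the exposure RR remains the average post effect.
4. Limit QIC, if kept, to age, sex and stage.

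The trial status section says data collection has not begun, so this is a change of wording only.

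The statistical cost should be disclosed. With 8 pre and 5 post quarters, a common start and equal weights, the variance factor for the status coefficient is 1/8 + 1/5 = 0.325 without time and 0.325 + 6.5²/52 = 1.1375 with linear calendar time. The SE is then √(1.1375/0.325) = 1.87 times as large. Calendar time alone also absorbs part of a ramp (about 1.07 against 1.20 for a 1.0 to 1.4 ramp). Adding centred time since implementation avoids that absorption on the log scale, at a factor of 0.325 + 6.5²/42 = 1.331, an SE 2.02 times that of status alone. The deferred power calculation should use whichever model is chosen.
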